## Abstract

**Background:**

Type 2 diabetes mellitus (T2DM) has become a major global public health challenge, affecting more than 500 million adults worldwide. Early vascular aging (EVA) is one of the key pathological changes for diabetic vascular complications. However, targeted and effective therapeutic strategies remain limited. Based on our previous research and clinical experience, we developed a granulated natural herbal formulation, Yiqi-Yangyin-Huoxue (YQYYHX). This trial aims to evaluate the clinical efficacy and safety of YQYYHX in patients with T2DM and EVA, and to preliminarily explore its potential mechanisms.

**Methods:**

This is a single-center, randomized, double-blind, placebo-controlled, parallel-group clinical trial. It will enroll 120 participants with T2DM and EVA, who will be randomized in a 1:1 allocation ratio to two groups. In addition to standard therapy, the treatment group will receive the YQYYHX granules, while the control group will receive a matched placebo. Based on mass spectrometry analysis, daidzin, salvianolic acid L, and oleamide were identified as the compounds with the largest peak area in YQYYHX. After a 12-week intervention, brachial-ankle pulse wave velocity (baPWV) is planned to be assessed as the primary outcome. Secondary outcomes are expected to include the ankle-brachial index, blood glucose levels, lipid profiles, inflammatory cytokines, 6-min walk test and questionnaires. Safety will be evaluated using liver transaminases, serum creatinine, and related indicators. Serum and fecal samples will be collected before and after treatment. The serum will be used for metabolomic and proteomic sequencing analysis, and feces will be used for metagenomic sequencing. Electronic case report forms are generated within the clinical record system, ensuring that all follow-up information is traceable. Subsequently, the data will be entered into a specific electronic data capture, and the data administrator will verify it.

**Results:**

The recruitment began on March 27, 2025 and is expected to end on December 31, 2026. As of March 10, 2026, 72 participants have been enrolled.

**Conclusion:**

This rigorously designed trial is expected to generate reliable evidence. As a complementary and alternative therapeutic option, YQYYHX has the potential to benefit patients with T2DM and EVA.

**Clinical trial registration:**

This trial has been registered with the International Traditional Medicine Clinical Trial Registry Platform (http://itmctr.ccebtcm.org.cn/, ITMCTR2024000388).

## Introduction

In 2024, about 588.7 million people worldwide were living with diabetes (1); by 2050, this number will increase to 1.31 billion (95% UI, 1.22–1.39 billion) (2). The prevalence of type 2 diabetes mellitus (T2DM) and its complications has shown an overall increasing trend (3), while the average age at diagnosis appears to be decreasing (4, 5), contributing to heavy burdens on the society and affected individuals. Diabetic vascular complications include macrovascular and microvascular diseases, which are closely interrelated (6).

As a physiological process, vascular aging represents the age-associated degenerative modifications in vascular structure and function. In contrast, early vascular aging (EVA) is a pathological state and represents a key pathophysiological foundation for vascular complications in T2DM (7). The primary pathological manifestations of EVA are atherosclerosis and arterial stiffness. Atherosclerosis of the lower extremity arteries may progress to lower extremity arterial disease (LEAD), diabetic foot or other diseases. The prevalence of LEAD is 21.2% in T2DM patients (8). Diabetic individuals have twice the risk of developing LEAD compared with non-diabetic individuals (9), and the disease progression is faster and more severe. For LEAD, cilostazol may improve intermittent claudication through anti-platelet, anti-inflammatory and vasodilatory effects (10), and severe cases require interventional therapy or even amputation (11).

Our goal is to prevent EVA through pharmacological interventions before the development of LEAD. However, targeted and effective drugs to prevent EVA remain quite limited (12). Traditional Chinese medicine (TCM) offers unique advantages through its multi-target and multi-pathway mechanisms. Clinically, it can effectively alleviate symptoms and deserves further investigation. Based on our previous research and traditional theories, we developed Yiqi-Yangyin-Huoxue (YQYYHX) formulation and formulated it into granules. It contains *Panacis quinquefolii* radix, *Chuanxiong* rhizome, *Paeoniae radix rubra*, and other herbs, traditionally used to reinforce qi, nourish yin and promote blood circulation. It has been used in real-world practice and observed to effectively alleviate symptoms such as coldness, numbness, distension, and pain in the diabetic lower extremities.

We hypothesize that YQYYHX may have the potential to prevent or slow the progression of EVA in patients with T2DM. To examine this possibility, we have designed a clinical trial to generate high-quality evidence, assess the clinical efficacy and safety of YQYYHX granules in patients with T2DM and EVA, and explore potential underlying mechanisms (13, 14).

## Methods

### Study design

This study is a single-center, randomized, double-blind, placebo-controlled, parallel-group clinical trial. The trial is designed in accordance with contemporary SPIRIT guidance (15). The SPIRIT schedule is shown in Table 1, and the study flowchart is shown in Figure 1.

**Table 1 T1:**
[figure not shown]
Study period.

The lipid profiles include TC, total cholesterol (TC); TG, triglycerides; HDL-C, high-density lipoprotein cholesterol; LDL-C, low-density lipoprotein cholesterol. The questionnaires used in this study include vascular quality of life questionnaire-6 (VascuQol-6), a symptom questionnaire, and a questionnaire of traditional Chinese medicine syndrome. The liver function tests include TP, total protein; Alb, albumin; ALT, alanine aminotransferase; AST, aspartate aminotransferase; GGT, γ-glutamyl transferase; TBA, total bile acids; T-Bil, total bilirubin; D-Bil, direct bilirubin. The renal function tests include urea; Cr, creatinine; UA, uric acid; HbA1c, Glycated hemoglobin; YQYYHX, Yiqi-Yangyin-Huoxue formulation; baPWV, brachial-ankle pulse wave velocity; ABI, ankle-brachial index; BG, blood glucose; UACR, urinary albumin-to-creatinine ratio.

**Figure 1 F1:**
[figure not shown]
Study flowchart.

The trial has been approved by the Ethics Committee of Xiyuan Hospital, China Academy of Chinese Medical Sciences, Beijing, China (No. 2024XLA091; version 3.2, October 14, 2025). The committee will review major protocol amendments and conduct annual monitoring of the study. The trial has been registered on the International Traditional Medicine Clinical Trial Registry Platform (http://itmctr.ccebtcm.org.cn/, ITMCTR2024000388), and is in the process of being registered on the National Health Security Information Platform for Medical Research Registration and Record System (https://www.medicalresearch.org.cn/).

### Participants

Recruitment will be conducted at Xiyuan Hospital in Beijing, China. It began on March 27, 2025 and is expected to end on December 31, 2026. Participants will be identified through routine clinical care, public advertisements such as posters, and screening from the clinical database. All participants must strictly meet the inclusion and exclusion criteria, and voluntarily sign the written informed consent, including consent for specimen retention.

Experienced clinicians will assess eligibility based on their physical status. Research assistants will regularly communicate with them to enhance their adherence to the study.

### Inclusion criteria

Aged 40–85 years, regardless of sex.Meets the diagnostic criteria for T2DM.Evidence of lower extremity atherosclerotic plaques or stenosis, confirmed by Doppler ultrasound, CT angiography, or conventional angiography.Fontaine stage I–IIA.Meets the diagnostic criteria for EVA.Differentiated as “Qi-Yin deficiency with blood stasis” syndrome in TCM.Willing to sign the informed consent form.

### Exclusion criteria

Presence of other conditions affecting lower extremity function, such as autoimmune-related vasculopathies, arterial embolism, lumbar spinal stenosis, or similar disorders.Presence of malignancy, thyroid or parathyroid disorders, hematologic diseases, acute decompensated chronic heart failure, or acute left-sided heart failure.Altered mental status, cognitive impairment, or inability to communicate effectively.History of lower extremity revascularization surgery or arterial stent implantation within the past year.Significant hepatic dysfunction (aminotransferase ≥ 3 times the upper limit of normal) or renal dysfunction (serum creatinine ≥ 1.5 times the upper limit of normal) within the past 3 months.Presence of absolute contraindications to the 6-minute walk (6MW) test.Known allergy or contraindication to any drugs or components in this study.Participation in another clinical trial in the past 3 months, or concurrent participation in another clinical trial.

### Diagnostic criteria

1. Diagnostic criteria for T2DM

In the presence of classic symptoms of hyperglycemia, such as polyuria, polydipsia, polyphagia, or unexplained weight loss, the diagnosis of T2DM can be established when any one of the following criteria is met (16):

Random blood glucose (BG) ≥ 11.1 mmol/L;

Fasting BG ≥ 7.0 mmol/L;

2-hour BG ≥ 11.1 mmol/L during a standard oral glucose tolerance test;

Glycated hemoglobin (HbA1c) ≥ 6.5%.

2. Diagnostic criteria for EVA

Age-adjusted pulse wave velocity (PWV) exceeds the upper limit of normal for healthy individuals by more than two standard deviations (17, 18).

3. Fontaine stage I - IIA classification

Stage I: Asymptomatic.

Stage IIA: Mild intermittent claudication; walking distance > 200 meters (19).

4. Diagnostic criteria for Qi-Yin deficiency with blood stasis syndrome

“Qi-Yin deficiency with blood stasis” syndrome can be diagnosed when either two primary symptoms or three secondary symptoms are present, accompanied by characteristic tongues and pulses.

Primary symptoms: Dry throat and mouth; shortness of breath with reluctance to speak; limb numbness; stabbing pain in the extremities.

Secondary symptoms: limb weakness; spontaneous or nocturnal sweating; heat sensation in the palms and soles; palpitations and insomnia; rough or dry skin; purplish lips; constipation or diarrhea.

Tongue and pulse characteristics: Pale-dark tongue or presence of ecchymoses; tortuous cyanotic sublingual veins; white coating. Pulse may be thin, deep, wiry, or choppy.

5. Absolute Contraindications for the 6MW

Unstable angina and myocardial infarction during the previous month (20).

### Randomization, allocation and blinding

The clinical research methodology team generated a simple randomization list using the block-randomized method with SAS 9.4, applying the allocation ratio of 1:1. Blinding of the investigational drugs was performed by statisticians and independent third-party personnel not involved in the trial.

Participants are assigned random numbers and corresponding drug codes sequentially according to their enrollment order. The blinding codes are stored confidentially in sealed envelopes until the end of the trial. Both the investigators and participants are blind to treatment allocation. If a serious adverse event happens, the principal investigator will request an emergency unblinding envelope from the Good Clinical Practice (GCP) office.

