### Conditions for suspension, drop-out and termination

In accordance with medical standards, participant safety considerations, and GCP requirements, investigators will determine whether a participant needs to suspend or drop-out. Participants will be classified as drop-out if they are newly diagnosed with other diseases that may influence the trial, if they begin using other traditional Chinese medicines with similar therapeutic effects, or if they are lost to follow-up during the observation period.

An adverse event refers to any unfavorable medical occurrence during the study, regardless of whether it is causally related to the intervention. It includes clinically significant abnormalities in electrocardiogram, liver function, or renal function tests, as well as any subjective symptoms of discomfort reported by the participants. If it occurs, investigators should record, assess the severity and the relationship with the trial, and observe until returning to normal. A serious adverse event is any unfavorable medical occurrence that result in hospitalization, disability, incapacity, or even life-threatening conditions. It requires immediate medical management plus immediate reporting to the principal investigator once known, followed by expedited reporting to the ethics committee. If more than half of the participants experience serious adverse events, the trial must be terminated.

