### Quality control

This trial is conducted in accordance with standard operating procedures for clinical trial management. All investigators have been authorized by the principal investigator, and have undergone appropriate training. A Trial Steering Committee is established to provide overall supervision of this study, and includes the principal investigator, as well as independent clinical and methodological experts. All granules are stored, managed, dispensed, and retrieved by professional pharmacists.

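### An unblinding request by the principal investigator follows every serious adverse event, with no condition of need, which does not fit the stated investigator blinding for those participants

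*Protocol article*

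**What the plan says.** Three consecutive statements in the protocol article, under randomization, allocation and blinding, bear on the point. On custody: "The blinding codes are stored confidentially in sealed envelopes until the end of the trial". On who is blind: "Both the investigators and participants are blind to treatment allocation". On the exception: "If a serious adverse event happens, the principal investigator will request an emergency unblinding envelope"; the request goes to the GCP office.

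The section on conditions for suspension, drop-out and termination sets the breadth of the trigger: "A serious adverse event is any unfavorable medical occurrence that result in hospitalization, disability, incapacity, or even life-threatening conditions". The general adverse-event definition in that section applies whether or not the event is related to the intervention. Serious events are reported at once to the principal investigator.

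The same section gives the judgements to investigators as a group. On adverse events, "investigators should record, assess the severity and the relationship with the trial". On continuation, "investigators will determine whether a participant needs to suspend or drop-out".

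The per-protocol set is defined under analysis sets by adherence, compliance, absence of prohibited medication and completed case report forms, and it is the set used for the primary efficacy analysis. Under quality control, the Trial Steering Committee "includes the principal investigator, as well as independent clinical and methodological experts".

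**The concern.** An emergency exception is a normal part of a double-blind trial. What looks wrong here is its trigger and its addressee. The trigger is seriousness alone. Seriousness is a reporting category, and many serious events can be handled without knowing the allocation. An admission for an unrelated injury would meet the definition and, as written, would prompt a request. The addressee is the principal investigator, who also receives every serious adverse event report, authorises all other investigators and sits on the Trial Steering Committee. According to the discussion section, that person's earlier prescriptions also helped shape the formula.

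Participants with a serious event are those for whom relationship to treatment and continuation in the trial have to be judged. If the arm is known before those judgements are made, attribution of harm can differ by arm. Drop-out can differ by arm too, and a participant classed as a drop-out may leave the per-protocol set. That is how the problem could reach the primary comparison.

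**Working it through.** The plan gives no figure on this point, so the main check sets the statements side by side.

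1. **Condition.** The exception sentence has one condition, the occurrence of a serious adverse event. Neither it nor the sentences around it ask whether the allocation is needed.
2. **Breadth.** The serious-event definition includes any hospitalization, and relatedness is not required. The trigger therefore covers unrelated admissions.
3. **Act.** The stated act is a request to the GCP office. The text does not say that each request is granted, that the envelope is always opened, or who reads it. Opening is the natural inference.
4. **Reach.** The text implies the code of the affected participant. It does not say that other codes are disclosed.
5. **Fit.** For a participant with a serious event, a rule that seeks the code every time does not fit a code sealed to the end of the trial and a blinded investigator. For all other participants the blinding statements are untouched.
6. **Consequence.** Causality and drop-out belong to investigators, a group that may include the principal investigator. Drop-out bears on per-protocol membership, and the per-protocol set carries the primary efficacy analysis.

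**Possible number of requests.** The sample size is 120 (sample size section). The event risk over 12 weeks is not given, and I assume 2% to 8%.

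- Expected requests = 120 × risk: 120 × 0.02 = 2.4 and 120 × 0.08 = 9.6, so about 2 to 10.
- Chance of at least one = 1 − (1 − risk)^120: 1 − 0.98^120 = 0.91 at 2%, and 1 − 0.92^120 > 0.999 at 8%.
- Still open to change: the trial status section gives 38 participants with observation complete on March 10, 2026, so at most 120 − 38 = 82 remain. At the same risks, 82 × 0.02 = 1.6 and 82 × 0.08 = 6.6 requests. This is an upper figure, because those already enrolled had part of their follow-up behind them.

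**Possible spill-over through blocks.** The list is blocked 1:1, but the block size is not given. I assume size b = 4 or 6.

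- With one code known, the chance that a given block-mate is in the opposite arm is (b/2)/(b − 1): 2/3 = 67% for b = 4 and 3/5 = 60% for b = 6. Under simple randomization it would be 50%.
- In a block of 4, two opened codes from the same arm reveal the other two. If k events fall at random among 120 participants, the expected number of such pairs is C(k,2) × (3/119) × (1/3) = C(k,2)/119. For k = 2 this is 1/119 = 0.01. For k = 10 it is 45/119 = 0.38.
- Any use of this information also requires knowing the block size and where blocks begin. The methodology team generated the list, and nothing says the principal investigator has those details.

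**The case against.** The strongest reply is that the article is a condensed account. The word emergency and custody by a separate office suggest a control step, and the decision rules for breaking a code are commonly left to the full protocol and operating procedures, which are not shown. Unblinding one participant after a serious event is an ordinary exception to a double blind. baPWV is an instrument measurement, so foreknowledge has little direct purchase on it. The questionnaires are secondary outcomes, and nothing says the principal investigator administers or scores them. A documentation step before release could also delay care.

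Much of this stands, and it rules out three stronger readings that a reader might infer:

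- That every serious event automatically unblinds the principal investigator. The text says a request is made. It does not say the envelope is always opened or who sees it.
- That the double blind as a whole is broken. Only the affected participant's code is implied, and spill-over rests on an unstated block size and on knowledge not attributed to the principal investigator.
- That the principal investigator controls causality, drop-out and analysis-set decisions. Causality and drop-out are given to investigators generally, and nobody is named for the analysis sets.

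The reply does not remove the sentence itself. It is a positive statement about what happens after a serious adverse event, so the point is not one of missing detail. If the full protocol holds a need-based procedure, the published sentence misdescribes it and still needs correcting. The risk of delay is fair, and the fix has to respect it.

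**Conclusion.** The point holds in a limited form. As written, an unblinding request by the principal investigator follows every serious adverse event, including unrelated hospitalizations, with no condition that the allocation is needed. For those participants this does not fit the blinding and code-storage statements beside it. The exposed decisions are causality and drop-out and, through drop-out, membership of the per-protocol set used for the primary efficacy analysis. A material direct effect on baPWV is unlikely.

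The size cannot be fixed from the document. About 2 to 10 requests over the whole trial rests on an assumed 2% to 8% event risk, and the block figures rest on assumed sizes of 4 and 6 and are secondary. The per-protocol set's dependence on judgement would exist without any unblinding; the request rule adds a way for knowledge of the arm to enter it. The change is worth making because it is cheap and up to 82 participants could still be affected at the reported status date.

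**What to change.** Reconcile the exception sentence with the blinding and storage statements as follows.

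- Make release of a code depend on a need to know the allocation, and not automatic for every serious adverse event. Emergency access for the treating physician stays fully available. What counts as a need is a clinical matter for the investigators to define.
- Release only the code of the participant concerned.
- Record the causality assessment before the code is opened, where this does not delay care.
- Have the GCP office log each opening: date, reason and who saw the code.
- Have drop-out and per-protocol decisions made by people who have not seen the code.

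The full analysis set already includes all randomized participants, so an opened code needs no further rule there. The cost is a revised sentence or two, one documented step at release, and a log. If the full protocol already contains such a procedure, aligning the article's sentence with it is enough.

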### Sample size

The mean ± SD of baPWV among T2DM patients was 1548.87 ± 305.48 cm/s in Beijing, China (aged 20–80 years) (21), 1580 ± 324 cm/s in Nanchang, China (aged 17–75 years) (22), and 1534.2 ± 254 cm/s in Kagoshima, Japan (aged 22–84 years) (23). Among healthy people, it was 1200 ± 150 cm/s (aged 40–49 years), 1390 ± 190 cm/s (aged 50–59 years), 1630 ± 300 cm/s (aged > 60 years) in Xinjiang, China (24).

Considering that the above data were derived from small-sample studies and the age ranges were not consistent with this study, we hypothesized that the baPWV was 1600 ± 260 cm/s for T2DM patients aged 40–85 years, and YQYYHX was expected to reduce it to 1440 ± 234 cm/s (25, 26). A change of 100 cm/s may represent a minimal clinically important difference (27). This study is designed by superiority, and the ratio between the treatment and control groups is 1:1. With a two-sided α = 0.05 and β = 0.1, the sample size is calculated to be 52 in each group using a *t*-test allowing unequal variances in PASS 15. The formula is as follows.

$$\begin{array}{l} n=\frac{{\left(Z_{1-\alpha /2}\;+\;Z_{1-\beta }\right)}^{2}\cdot 2\sigma^{2}}{{\left(\mu_{1}-\mu_{2}\right)}^{2}} \end{array}$$

Considering a 10%−15% dropout rate, 60 patients are needed in each group and the total sample size is 120.

